### Sample size

Based on data from the literature, we estimate that 35% of patients in the placebo group will develop BK viruria by 1-year post-transplantation
[24]. In order to detect an absolute reduction in BK viruria of 20% (from 35 to 15%) with a two-sided alpha error of 0.05, a beta error of 0.2 and a 5% loss to follow-up rate, we would need 154 patients in total (77 per group). The minimal clinically important difference of 20% was justified based on a survey of experts from the Canadian Renal Transplant Study Group. The investigators wanted to see a substantial effect on viruria in order to justify proceeding with a larger trial examining the more clinically relevant endpoint of time to doubling serum creatinine, transplant failure or death.

### Statistical analysis

Baseline characteristics of patients in the two treatment arms will be assessed using frequency distributions and univariate descriptive statistics, including measures of central tendency and dispersion. Analyses will be performed by intention-to-treat. Since this is a pilot study to assess biologic efficacy, the intention-to-treat analysis will be supplemented by a sensitivity analysis that excludes patients who did not complete the allocated treatment plan. The primary analysis will use a nonparametric log-rank test, stratified by center, to compare the time to occurrence of BK viruria between the control and levofloxacin treatment groups. Kaplan-Meier survival curves will also be plotted to visually assess differences in incidence over time.

For secondary safety outcomes, the proportion of adverse events occurring in each treatment arm will be compared using an unadjusted chi-square test or Fisher’s exact test if cell sizes are small. We will evaluate overall adverse events as well as specific serious adverse events (for example *C difficile*-associated diarrhea). For the secondary feasibility outcome of recruitment, we will calculate the proportion (and 95% confidence interval) of all patients transplanted during the recruitment period who are randomized into the trial. In addition, we will calculate the proportion of patients that are eligible but consent declined, eligible but not approached and not eligible. These analyses will be performed at each site and for the trial overall. For the secondary feasibility outcomes of adherence, non-study quinolone use, drop-out and loss to follow-up, the proportion of each outcome will be compared between the arms with an unadjusted chi-square or Fisher’s exact test. Since this is a pilot study, we have not planned for any formal interim analyses.

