**Methods/design:**

The aim of this pilot trial is to assess the efficacy, safety and feasibility of a 3-month course of levofloxacin in the kidney transplant population. This is a multicenter, randomized, double-blind, placebo-controlled trial with two parallel arms conducted in 11 Canadian kidney transplant centers. A total of 154 patients with end-stage renal disease undergoing kidney transplantation will be randomized to receive a 3-month course of levofloxacin or placebo starting in the early post-transplant period. Levofloxacin will be administered at 500 mg po daily with dose adjustments based on kidney function. The primary outcome will be the time to occurrence of BK viruria within the first year post-transplantation. Secondary outcomes include BK viremia, measures of safety (adverse events, resistant infections,*Clostridium difficile*-associated diarrhea), measures of feasibility (proportion of transplanted patients recruited into the trial), proportion of patients adherent to the protocol, patient drop-out and loss to follow-up,and use of quinolone antibiotics outside of the trial protocol.

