### Other trial maneuvers

Outside of the primary trial intervention, the only major interventions that are being controlled are CMV and *Pneumocystis jirovecii* infection prophylaxis. All participants are receiving prophylaxis against CMV and *Pneumocystis* based on established guidelines
[29,30]. Consistent with current clinical practice, patients with a significant unexplained and sustained increase in serum creatinine undergo transplant biopsy. A set protocol has been developed outlining when study medication must be stopped (for example significant *Clostridiumdifficile*-associated diarrhea, rash, tendonitis). Co-interventions that might influence BK infection, such as immunosuppressive medication use, are being thoroughly documented but not controlled. Although immunosuppressive strategies are somewhat variable between centers, mandating a strict immunosuppressive regimen would have limited site participation and generalizability of study findings. More importantly, all immunosuppressive medications have been associated with BK virus infection and the net state of immunosuppression appears more important than individual agents
[6,31].

As per our eligibility criteria, the routine use of quinolones for bacterial prophylaxis (for example urinary tract infection (UTI)) is not permitted. The investigators have agreed to not use quinolones for empiric antibiotic therapy. If a quinolone is absolutely necessary, then investigators have this option for the safety of the patient. We expect this situation to be rare given the choices of antibiotics available (for example cephalosporins, amoxicillin/clavulanic acid, nitrofurantoin). A set protocol has been developed to guide the sites on non-study use of quinolones. Once cultures are available, patients are switched to a non-quinolone regimen. If the infection is only quinolone-sensitive or the patient is intolerant/allergic to other antibiotics, then quinolone use (beyond 24 to 48 hours) is allowed. During this time, study medication (placebo or levofloxacin) is withheld. All non-study use of quinolones is being thoroughly documented.

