### Protecting against bias

Patients are randomized using a web-based system. A permuted blocked randomization method stratified by center is used to allocate patients. An independent statistician has generated the randomization scheme. The randomization process consists of a computer-generated random listing of the treatment allocations stratified by center in variable permuted blocks of 2 and 4. Only the independent statistician and designated research pharmacist at the coordinating center has knowledge of the randomization codes to ensure concealed randomization of the patients. After screening the patient for eligibility and obtaining informed consent, the study coordinator accesses the trial website and provides the subject’s unique identification,as well as a confirmation of consent and eligibility. The website returns the next available randomization number.

In order to minimize selection and ascertainment biases, physicians, nurses, investigators and research staff are blinded to the randomization schemes and treatments administered. The study medication and placebo are identical in appearance. The designated research pharmacist at the coordinating center is expressly forbidden to discuss individual treatment allocation with the study team or any patients. In addition, the staff at the central laboratory performing the BK virus measurements are not aware of the patient’s treatment allocation. Given that this trial is blinded, contamination and co-interventions should not become imbalanced between the treatment arms. We are documenting the use of co-interventions that may have some impact on BK virus, such as immunosuppressive drug selection, dose and levels
[6], leflunomide
[6,32], cidofovir
[6,33], and intravenous immunoglobulin
[6,34].

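### The between-arm safety and feasibility tests leave out center, although allocation and the primary test are stratified by it: valid, but somewhat conservative if event rates differ between centers

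*Protocol article*

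**What the plan says.** The abstract describes a trial "conducted in 11 Canadian kidney transplant centers". Under Protecting against bias, allocation is a "computer-generated random listing of the treatment allocations stratified by center in variable permuted blocks of 2 and 4". Under Statistical analysis, "The primary analysis will use a nonparametric log-rank test, stratified by center". The next paragraph of that section drops center. On safety it states that "the proportion of adverse events occurring in each treatment arm will be compared using an unadjusted chi-square test". Small cells go to Fisher's exact test instead. Four feasibility outcomes (drop-out, loss to follow-up, adherence, and quinolones taken outside the study) are treated alike: "the proportion of each outcome will be compared between the arms with an unadjusted chi-square or Fisher’s exact test". Recruitment is only estimated, as a proportion with a 95% confidence interval, and the arms are not compared on it. The lack of adjustment is written into the text, so it is a stated choice and not a detail left to a fuller document.

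**The concern.** Blocking within center keeps the arms nearly balanced in every center, so differences between centers largely cancel out of the arm comparison. An unadjusted test still counts those differences in its variance. If center predicts the outcome, the standard error is too large and the true type I error falls below 5%. For a harm comparison this is the unhelpful direction, because a real excess on levofloxacin becomes harder to show. Safety is one of the pilot's three aims, and the sample size was set for viruria alone. The article gives some reason to expect center differences: "Although immunosuppressive strategies are somewhat variable between centers", and these strategies are recorded but not controlled. It gives no reason for using center in the primary test and leaving it out of the others.

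**Working it through.** **1. The plan's own figure.** Inputs from Sample size: 35% v 15%, two-sided alpha 0.05, power 0.80, 5% loss.

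n per arm = [1.960·√(2·0.25·0.75) + 0.842·√(0.35·0.65 + 0.15·0.85)]² / 0.20² = 72.4, so 73. Then 73/0.95 = 76.8, so 77 per arm and 154 in total. The stated size reproduces. It rests on the viruria outcome and says nothing about power for safety.

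**2. Size of the conservatism in closed form.** Let p be the overall event rate and V the variance of the true rates between centers. The unadjusted test uses about p(1−p) per patient. With balance within center, the arm difference varies only with p(1−p) − V. The ratio is r = 1 − V/[p(1−p)], and the true two-sided type I error is about 2·[1 − Φ(1.96/√r)]. V is not in the documents. I assume center effects that are normal on the logit scale, centered so that the average rate is p.

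| p | SD | V | r | type I error |
|---|---|---|---|---|
| 5% | 0.5 | 0.0006 | 0.987 | 4.9% |
| 5% | 1.0 | 0.0028 | 0.942 | 4.4% |
| 20% | 0.5 | 0.0062 | 0.962 | 4.6% |
| 20% | 1.0 | 0.0214 | 0.866 | 3.5% |
| 50% | 0.5 | 0.0140 | 0.944 | 4.4% |
| 50% | 1.0 | 0.0434 | 0.827 | 3.1% |

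With V = 0, r = 1 and nothing is lost.

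**3. Simulation.** 154 patients, 11 centers, blocks of 2 and 4. Centers were even (14 each) or uneven (40 down to 3). There were 8000 null and 4000 alternative replicates per setting. The assumed odds ratios were 4, 2.7 and 2.6 at control rates of 5%, 20% and 50%. Monte Carlo error is about 0.25 points for type I error and 0.7 points for each power. CMH is the Cochran-Mantel-Haenszel test stratified by center.

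| Control rate | SD | Power, chi-square v CMH, even | Power, chi-square v CMH, uneven |
|---|---|---|---|
| 5% | 0 | 71.3 v 71.0 | 71.4 v 70.6 |
| 5% | 0.5 | 68.0 v 68.5 | 68.6 v 68.4 |
| 5% | 1.0 | 60.8 v 63.0 | 60.2 v 61.8 |
| 20% | 0 | 79.3 v 79.4 | 78.1 v 77.8 |
| 20% | 0.5 | 75.1 v 76.2 | 75.4 v 76.3 |
| 20% | 1.0 | 65.3 v 70.9 | 67.1 v 71.1 |
| 50% | 0 | 81.0 v 80.5 | 81.5 v 80.8 |
| 50% | 0.5 | 79.2 v 80.4 | 78.2 v 79.0 |
| 50% | 1.0 | 67.3 v 73.6 | 67.8 v 73.4 |

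- Gain from CMH at SD 0: −0.8 to +0.1 points.
- Gain at SD 0.5: −0.2 to +1.2 points.
- Gain at SD 1.0: +1.6 to +2.2 points at 5%, and +4.0 to +6.3 points at 20 to 50%.
- Type I error of chi-square at SD 1.0: 4.4% (5% rate), 3.4 to 4.0% (20%) and 3.0 to 3.2% (50%), in line with step 2. CMH stays at 4.4 to 5.5% throughout.
- A separate run at an assumed 30% rate gave gains of 2.0 points at SD 0.5 (78.2 v 80.2) and 6.6 points at SD 1.0 (67.8 v 74.4).

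**4. Uncommon events, exact tests.** Fisher against the exact center-stratified test at an assumed 5% rate and odds ratio 4 (even centers, 3000 replicates) gave power of 64.2 v 63.8% at SD 0, 67.1 v 67.4% at SD 0.5 and 66.6 v 69.6% at SD 1.0. With uneven centers the gain at SD 0.5 was 1.5 points. Levels differ between runs, so only differences within a run should be read. Type I error in this run was 1.6 to 2.7% for both tests. In step 3, Fisher was already at 2.1 to 2.2% with no center effect at all, so that shortfall comes from discreteness and not from the blocking.

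**The case against.** The other side has a good case. Unadjusted tests keep type I error at or below 5%, and simple comparisons of secondary proportions are common in a pilot. The article calls only immunosuppressive strategy variable, and only somewhat. It also says that the net state of immunosuppression seems to matter more than the individual agents. Nothing shows that infection, rejection or *C difficile* rates differ by center.

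The larger losses need a wide spread. Around a 30% rate, 95% of centers would lie between about 14% and 53% at SD 0.5, and between about 6% and 75% at SD 1.0. SD 0.5 is already sizeable, and the loss there is close to simulation noise. All of this stands. It limits the size of the point but does not remove it, because stratifying costs almost nothing when center has no effect.

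A reader might go further than the documents allow in four ways:

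- **The tests are conservative as they stand and likely to miss a harm.** That holds only if center is prognostic, and for uncommon harms the effect is small.
- **The safety confidence intervals are too wide.** The article specifies none for a between-arm comparison.
- **All feasibility results are affected.** Recruitment has no arm comparison, and the criterion of more than 75% adherent is an overall proportion.
- **The decision to progress is at risk.** The article ties that to viruria and urine viral load. The viruria test is already stratified, and no safety p-value is named as a threshold.

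**Conclusion.** The point holds as a minor matter of efficiency and consistency. The plan stratifies by center in allocation and in the primary test, then leaves center out of the between-arm tests for adverse events, adherence, non-study quinolone use, drop-out and loss to follow-up. No result would be invalid. If event rates differ between centers, the unadjusted tests give up about 0 to 2 power points at a logit SD of 0.5. At SD 1.0 they give up about 4 to 6 points for events at 20 to 50%, with one run at 30% slightly higher. For events near 5% the loss is about 0 to 3 points. The center spread, center sizes, event rates and odds ratios are all assumptions. The direction of the effect is secure, but its size in this trial is unknown and could be nil.

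**What to change.** In Statistical analysis, replace the unadjusted chi-square or Fisher test with a Cochran-Mantel-Haenszel test stratified by center, using the exact conditional version when cells are small. Apply it to adverse events (overall and specific) and to the between-arm comparisons of adherence, non-study quinolone use, drop-out and loss to follow-up. Report the center-stratified (Mantel-Haenszel) risk difference with a 95% confidence interval, and keep the unadjusted counts in the tables. The recruitment proportion and the overall adherence criterion need no change.

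The change is a sentence or two of wording and needs no new data, since center is already used in the primary test. Centers with no events, or with patients in one arm only, contribute nothing to the stratified test. In the simulations with no center effect, including centers as small as 3 patients, this cost less than 1 power point.

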## Discussion

BK virus infection has emerged as a major complication in kidney transplantation. There are no proven strategies to prevent or treat BK virus infection. This trial will assess the efficacy, safety and feasibility of a 3-month course of levofloxacin to prevent BK virus infection following kidney transplantation. While there are concerns about possible antimicrobial resistance and complications, such as *C difficile*-associated diarrhea, we are closely monitoring safety and adverse events as part of this trial. Results from this pilot study will provide vital information to design and conduct a large, multicenter trial to determine if levofloxacin therapy decreases major clinical outcomes, such as biopsy-proven BK nephropathy or graft loss in kidney transplantation. If levofloxacin significantly reduces BK viruria and urine viral loads in kidney transplantation, it will provide strong support of biologic effect and justification to progress to the larger trial. If the full trial shows that levofloxacin significantly reduces BK infection and improves outcomes, the use of this preventive therapy will be a major innovation in the management of kidney transplant recipients, especially given the lack of proven therapies for this condition.

## Trial status

The first participant was randomized in December 2011 and recruitment is ongoing as of 28 May 2013.

## Abbreviations

CMV: *Cytomegalovirus*; NIH: National Institutes of Health; PCR: Polymerase chain reaction; qPCR: Quantitative real-time PCR; RCT: Randomized controlled trial; UTI: Urinary tract infection.
